## Abstract

**Background:**

Over recent decades there has been a substantial increase in asthma and allergic disease especially in children. Given the high prevalence, and the associated high disease burden and costs, there is a need to identify effective strategies for the primary prevention of asthma and allergy. A recent systematic review of the literature found strong supportive epidemiological evidence for a protective role of the Mediterranean diet, which now needs to be confirmed through formal experimental studies. This pilot trial in pregnant women aims to establish recruitment, retention and acceptability of a dietary intervention, and to assess the likely impact of the intervention on adherence to a Mediterranean diet during pregnancy.

**Methods/Design:**

This study was a pilot, two-arm, randomised controlled trial in a sample population of pregnant women at high risk of having a child who will develop asthma or allergic disease.

**Discussion:**

The work ultimately aims to contribute to improving health outcomes through seeking to reduce the incidence of asthma and allergic problems. This pilot trial will prove invaluable in informing the subsequent planned large-scale, parallel group, randomised controlled trial.

**Trial registration:**

ClinicalTrials.gov: NCT01634516

## Background

In recent decades, there has been a marked worldwide increase in asthma and allergic disease prevalence, especially in children [1,2]. Children bear the greatest burden of asthma and allergic disease, principally atopic dermatitis/eczema, allergic rhino-conjunctivitis and food allergy [3]. Asthma is a major public health concern – the World Health Organization estimates that globally 235 million people currently have asthma and that it is now one of the most common childhood diseases requiring chronic drug therapy [4].

Estimates state that in the UK 1.1 million children and 4.1 million adults receive treatment for asthma. The cost of asthma for the UK economy was estimated to be £2.3 billion in 2001, comprising £1.2 billion in lost productivity and £889 million in National Health Service (NHS) expenditure [5,6]. The UK prevalence of atopic dermatitis/eczema and hay fever in children is also high, such that internationally the UK was ranked second for prevalence of atopic dermatitis/eczema and seventh for hay fever [7,8]. In Scotland in 2004, nearly 4% of general practitioner consultations and 1.5% of hospital admissions were for allergic disorders [9].

There is increasing evidence suggesting that prenatal and early-life exposures influence the development of asthma and allergic diseases, with interest converging on the possible role of the diet during pregnancy and early life. It has been hypothesised that the maternal diet during pregnancy modulates the development of asthma and allergic disease by influencing foetal airway and/or immune development [10]. Birth cohort studies have reported associations between aspects of maternal diet during pregnancy and childhood asthma and allergic outcomes [11]. A recent systematic review and meta-analysis examined the strength of the scientific evidence for associations between dietary intake of foods and nutrients by pregnant women and children, and the risk of children developing asthma and other allergic disorders [12]. Of nearly 15,000 potentially relevant articles, 62 satisfied the inclusion criteria. There were no randomised controlled trials (RCTs); all were cohort, case–control or cross-sectional studies. Although these study designs are potentially at high risk of bias in assessing the effectiveness of dietary constituents/patterns, the review results found a potentially substantial protective role for vitamins A, D and E, zinc, fruit and vegetables, and a Mediterranean diet (MD) for the prevention of asthma and allergic disorders. Of these dietary candidates, vitamin D [13] and vitamin E [14] are under investigation. In general, the MD is characterised by the elevated intake of fruits and vegetables, olive oil, legumes, nuts and fish [15]. The study of dietary patterns represents a broader picture of food and nutrient consumption compared with single food items and nutrients [16,17].

Of the five observational MD studies in the review, one used a cohort design [16] and four were cross-sectional studies [18-21]. The higher quality cohort study reviewed by Nurmatov and colleagues [12] reported that high adherence to a MD was found to be protective against persistent wheeze (odds ratio = 0.22, 95% confidence interval = 0.08, 0.58), atopic wheeze (odds ratio = 0.30, 95% confidence interval = 0.10, 0.90) and atopy (odds ratio = 0.55, 95% confidence interval = 0.31, 0.97) [16]. There are large geographical differences in the prevalence of asthma, with higher prevalence rates in English-speaking countries and lower prevalence rates in, for example, the Mediterranean region [22,23]. As a result of a high intake of olive oil, vegetables and fruit, wholegrain cereals and bread, a low intake of dairy products, some fish consumption, and only small amounts of red meat, a MD is rich in antioxidants but also high in carbohydrates, fibre and unsaturated fatty acids and low in saturated fatty acids.

Whilst observational studies have reported potentially beneficial associations with a MD, it is not known whether an intervention to promote the MD reduces the likelihood of childhood asthma and allergic disease. There are currently no RCTs testing the hypothesis that a MD decreases the risk of asthma and allergic disease in children. Before testing this hypothesis in a large-scale RCT, pilot work is needed to ensure there is a robust measure to assess the MD and to investigate the feasibility of achieving and sustaining a dietary change. We are carrying out a pilot trial of an intervention to promote a MD, to inform a subsequent multi-centre RCT. We report here the protocol for the pilot trial in a sample of pregnant women.

### Aims of the study

The primary aims of the pilot trial are to investigate rates of maternal recruitment and retention in the control and intervention groups, and to assess the acceptability of dietary advice and dietary modifications in the intervention group.

The secondary aims are to determine whether there are measurable changes in the MD score in both groups, and to measure adherence to a MD during the last trimester of pregnancy in the intervention group.

### Specific research questions

The research questions are as follows: What are the recruitment and retention rates of pregnant mothers whose infants are at high risk of asthma/allergy? To what extent do mothers adhere to a MD? Can a MD score be increased in pregnancy? Can any increases in MD adherence be sustained during pregnancy? Can a measurable change in a biomarker of oxidative stress be detected as a result of adherence to a MD? Is the advice and dietary modification acceptable to participants? To inform cost-effectiveness considerations, can a breakdown of intervention delivery time (initial contact and number and duration of follow-up telephone calls) be measured?

## Methods/Design

### Ethical and research and development approval

A favourable ethical opinion was obtained from the NHS Lothian South East Scotland Research Ethics Committee 02 on 12 April 2012 (REC reference 12/SS/0052). NHS Lothian R&D Management Approval was obtained on 27 April 2012 (R&D No. 2012/SJ/DN/01).

### Trial design

We are carrying out a two-arm, pilot, parallel-group RCT. Trial participants are being recruited from two maternity service sites in Scotland, both with dating scan appointment rates of approximately 100 per month. Eligible participants receive either: diet advice and support, with a supporting MD resource booklet, in addition to standard care; or standard care with no additional dietary advice/support/materials.

### Eligibility of participants entering the trial

#### Inclusion criteria

The inclusion criteria are as follows: pregnant in first trimester; age ≥16 years; a history of atopic dermatitis/eczema, food allergy, allergic rhinitis (persistent or intermittent) or asthma in the pregnant woman, her partner, or children; and willing to give informed consent.

#### Exclusion criteria

The exclusion criteria are as follows: not pregnant; age <16 years; no history of atopic dermatitis/eczema, food allergy, allergic rhinitis (persistent or intermittent) or asthma in the pregnant woman, her partner, or children; recent (within the last 3 months) or current involvement in a dietary or supplementation trial; and unable/unwilling to give informed consent.

### Recruitment

#### Hospital/community treatment centre

We have recruited one hospital and one community treatment centre in the same NHS Scotland Board/region that carry out dating scans.

#### Participants

A letter of invitation to join the pilot trial, information for participants and a consent form are being sent out to women along with their dating ultrasound scan appointment letter and pack. These are sent by a health records department running a centralised regional telephone booking system and booking clerks are keeping a record of invitations sent. Interested participants are invited to contact the researcher by text, telephone or email to discuss the trial. They are then screened for eligibility to take part in the trial. Eligibility of women at high asthma/allergic risk for the foetus is based on a positive answer to the question: ‘Do you (the mother), or the father, or sibling of the baby have an allergic disease: eczema, a food allergy, hay fever or asthma?’ Details are recorded on the screening questionnaire.

Enrolled participants are sent a food frequency questionnaire (FFQ; Scottish Collaborative Group Food Frequency Questionnaire version 6.6) for completion at home and a small urine collection vessel with instructions to fill the container on the day of the scan and bring that, the consent form and the completed FFQ to their ultrasound scan appointment. The researcher then arranges to meet the participant in the clinic waiting area after their dating scan, where the researcher collects the consent form, urine sample and FFQ and administers a baseline MD questionnaire (based on [18]). Urine specimens are being stored frozen at -80°C for subsequent analysis.

There are two further opportunities for recruitment. First, following invitation, when nonresponders arrive in the clinic they may see a poster in the clinic advertising the study. If they would like to take part they can ask the clinic staff to point out the researcher to them. If the potential participant has already read the information for participants then they are able to consent and can be recruited after the dating scan that day. Second, those who are interested, but have not read the information for participants are given a further period of time (that is, ≥24 hours) before being contacted by the researcher to see whether they wish to participate; if recruited and randomised to the intervention group, the participant is asked to return to the hospital for the intervention or alternatively the researcher can arrange a home visit.

Consent is obtained to inform the participants’ general practitioner of her participation in the trial, and a letter is subsequently sent to the general practitioner.

### Randomisation

Participating women are randomised when visiting the hospital for their dating ultrasound scan. Allocation to the intervention arm or control arm is by restricted randomisation (by site), via pre-randomised sealed envelopes, based on a predetermined random number allocation. This randomisation has been carried out by an independent statistician. Participants are randomised after consent has been obtained and immediately after the first MD questionnaire has been completed. Participants are enrolled for a total of ~6 months (that is, from 12 to 36 weeks of pregnancy).

### Intervention

The intervention is a 15-minute structured dietary advice session encouraging the consumption of particular foods that are consistent with the MD, developed with a dietitian and administered by a researcher or hospital dietitian using a booklet. The initial session is directed at increasing consumption of MD foods, with subsequent supportive telephone calls from the dietitian/researcher at 4, 8 and 18 weeks post enrolment, to review and revise MD goals. The booklet contains text and pictures, with frequently asked questions and answers and ideas for modifying the diet, such as eating more fruit, vegetables, using olive oil and eating more fish. Advice for cutting back on fat on meat is also included. A MD pyramid (adapted from [24]) is contained in the booklet and discussed. The dietitian/researcher also discusses ideas for participants to reach the goals of eating more fruit, vegetables and fish in the context of current portion consumption, and reducing red and processed meat by exchanging with white meat. The use of olive oil for cooking and dressings is encouraged, and participants are given a shopping voucher (£10) at baseline and 12 weeks post baseline that can be used for purchasing olive oil. Olive oil used for cooking and dressings is an important component of the MD. The MD booklet also has recipes for a soup, a fresh sauce and a vegetable curry, all of which have olive oil as an ingredient. No energy restrictions are suggested, and the target of at least five portions of fruit and vegetables per day is emphasised.

#### Intervention arm

After the dating scan the researcher collects the consent form, the FFQ and the urine sample and checks that the participant has previously received standard dietary advice for pregnant women, including the importance of folic acid and vitamin D supplementation. Participants then receive a 15-minute dietary advice session. A supermarket voucher to the value of £10 is provided.

At 12 weeks post-baseline, a second MD questionnaire with a reply envelope for completion and return is posted to the participant and followed up by a telephone call from the researcher. A further supermarket voucher to the value of £10 is sent to the participant on receipt of the completed questionnaire, accompanied by advice to use it to buy olive oil. Non-returns of diet questionnaires are followed up by a telephone enquiry from the researcher after 1 week, with a reminder letter and another questionnaire being sent out after 2 weeks without a response.

Two weeks before the 24 weeks post-baseline MD questionnaire, participants are contacted by telephone to arrange a home visit and are sent a second FFQ. When visited at home by the researcher, a third MD questionnaire and second FFQ and a urine sample are collected.

Free telephone access to the researcher is available throughout the study; the frequency and duration of calls to the researcher are being recorded.

#### Control arm

After the dating scan the researcher collects the consent form, the FFQ and the urine sample and checks that the participant has previously received standard dietary advice for pregnant women, including the importance of folic acid and vitamin D supplementation. These participants do not receive the 15-minute dietary advice session. A supermarket voucher to the value of £10 is provided. The first follow-up by the researcher is by telephone 12 weeks post-baseline to inform them they will receive the second MD questionnaire and reply envelope for completion and return. A further supermarket voucher to the value of £10 is sent to the participant on receipt of the completed questionnaire. Non-returns of diet questionnaires are followed up by a telephone enquiry from the researcher after 1 week, with a reminder letter and another copy of the questionnaire being sent out after 2 weeks without a response.

Two weeks before the 24 weeks post-baseline MD questionnaire, participants are contacted by telephone to arrange a home visit and are sent a second FFQ. When visited at home by the researcher, a third MD questionnaire and second FFQ and a urine sample are collected.

### Assessment of outcomes

#### Recruitment and retention

The number of women who received an invitation, responded, were eligible, were recruited and completed the trial will be recorded.

#### Measuring the Mediterranean diet score

The MD score is being measured at baseline (around 12 weeks of pregnancy) and at 12 and 24 weeks post baseline MD questionnaire (i.e. approximately weeks 24 and 36 of pregnancy). The number of times participants consume particular food groups in the last week is classified into never, one or two times, or three or more times. For beneficial components (for example, vegetables, legumes, fruits, cereals, fish, dairy products) the frequency scoring is higher than for components considered less beneficial (meat, fast food, confectionery). As our trial involves pregnant women, we assume dairy products to be protective and we will not include alcohol consumption in the score [16]. This is because of the increased requirement for calcium and the fact that alcohol consumption is not recommended in pregnancy. A 3-point increase in MD score on a scale of 22 could equate to potentially moving from a low-quality maternal MD score into the optimal range of MD score based on the study of Chatzi and colleagues [16].

#### Biomarker analysis

Urine samples are being collected from participants at baseline and 24 weeks post intervention. We will measure levels of urinary 8-hydroxy-2′-deoxyguanosine, the ratio of nitrite to nitrate, and ferric-reducing antioxidant power. Urinary 8-hydroxy-2′-deoxyguanosine is a sensitive, stable and integral marker of oxidative stress *in vivo*[25]. The stable metabolic products of nitrous oxide and nitrite/nitrate are markers of whole-body nitrous oxide production. Total antioxidant activity is measured by the ferric-reducing antioxidant power. These analytes will be used as outcome measures in order to relate changes in oxidative stress, activity and nitrous oxide production to changes in MD score.

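### The urinary nitrite-to-nitrate ratio is listed as the measurement but is to be read as gas production, and a ratio alone does not identify an amount

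*Protocol article*

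**What the plan says.** All of this comes from the protocol article, mainly the section Biomarker analysis under Assessment of outcomes.

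- **Measurement.** Three urinary measures are listed: 8-hydroxy-2′-deoxyguanosine, then "the ratio of nitrite to nitrate, and ferric-reducing antioxidant power". No separate nitrite level, nitrate level, total or dilution measure is named.
- **Interpretation.** A later sentence says that "nitrite/nitrate are markers of whole-body nitrous oxide production". Its subject joins the metabolic products of the gas with nitrite/nitrate, as if they were two different things, and its verb is plural.
- **Use.** The analytes are outcome measures, intended to "relate changes in oxidative stress, activity and nitrous oxide production to changes in MD score".
- **Sampling.** "Urine samples are being collected from participants at baseline and 24 weeks post intervention". For the first sample, the Participants section describes "a small urine collection vessel with instructions to fill the container on the day of the scan". No timed collection is described.
- **Diet.** The Intervention section has participants discuss how to "reach the goals of eating more fruit, vegetables and fish in the context of current portion consumption". The food frequency questionnaire (FFQ) is collected at baseline and at the 24-week home visit, the same two points as the urine.

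**The concern.** The quantity measured and the quantity interpreted are not the same kind of thing. Whole-body production is an amount. A ratio of two end-products describes their relative size, and common movement in both drops out of it. The article gives no reason why the ratio should index an amount, and it names no other quantity for the purpose.

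At stake is what this outcome can conclude. A real change in production could leave the ratio where it was, and a change in the ratio could come from something other than production. The planned comparison is with the Mediterranean diet (MD) score, which counts vegetables among its beneficial components. If dietary nitrate reaches the urine (an assumption; the article does not discuss it), an association between ratio and MD score could arise from intake alone.

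**Working it through.** The article gives no figure for this biomarker, so there is nothing to reproduce. The check is algebraic, with illustrative constants.

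**Set-up.** Let P be production, D urine dilution, and B nitrate from any source other than production. Take

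- nitrite = aP / D
- nitrate = (bP + B) / D

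Then ratio = aP / (bP + B), and total = (aP + bP + B) / D. The constants a = 0.02 and b = 1 are assumptions; the article gives no concentrations.

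**1. Both products proportional to production (B = 0).** The ratio reduces to a/b, which does not contain P. In raw numbers, 1/50 = 2/100 = 4/200 = 0.02, with totals of 51, 102 and 204.

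**2. Proportionality relaxed.** This was done by adding a fixed background B to nitrate, or by letting nitrite and nitrate follow different powers of P. With D = 1:

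| Case (assumed) | Ratio at P = 0.5, 1, 2 | Total at P = 0.5, 1, 2 |
|---|---|---|
| B = 0 | 0.0200, 0.0200, 0.0200 | 0.51, 1.02, 2.04 |
| B = 0.5 | 0.0100, 0.0133, 0.0160 | 1.01, 1.52, 2.54 |
| B = 2 | 0.0040, 0.0067, 0.0100 | 2.51, 3.02, 4.04 |
| Powers 1 (nitrite) and 0.8 (nitrate) | 0.0174, 0.0200, 0.0230 | not needed |
| Powers 0.8 (nitrite) and 1 (nitrate) | 0.0230, 0.0200, 0.0174 | not needed |

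The ratio now moves with production, but it does not say how much was produced. A ratio of 0.0100 occurs at P = 0.5 with B = 0.5 and at P = 2 with B = 2, a fourfold difference in production. In the last two rows the same rise in production moves the ratio in opposite directions.

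**3. More nitrate with production unchanged.** If nitrate rises by 50% and nitrite stays the same, the ratio becomes 1/1.5 = 0.667 of its starting value, a fall of 33% whatever the start. The total rises as well:

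- starting at 1:100, from 1010 to 1510, or 500/1010 = +49.5%
- starting at 1:50, from 1.02 to 1.52, or 0.50/1.02 = +49.0%
- starting at 1:10, from 11 to 16, or 5/11 = +45.5%

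So neither quantity separates intake from production.

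**4. Urine dilution.** With P = 1 and B = 0, doubling D leaves the ratio at 0.02 but takes the total from 1.02 to 0.51. At P = 2 and D = 2 the total is 1.02 again, the same as at P = 1 and D = 1. An unscaled total from an untimed specimen therefore does not identify production either.

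**The case against.** The strongest reply is that the marker sentence uses a plural verb and can mean the two products rather than their ratio, so this may be loose wording. That reading is open. It does not settle the matter, because the measurement sentence names a ratio. Under that reading the two sentences disagree about what the outcome is.

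Several other points on that side stand in full:

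- Exact cancellation requires both products to be proportional to production, which the article does not state. Step 2 shows that the ratio can respond when they are not.
- A reader might infer that production-related quantities can no longer be obtained. The article does not support that: both components must be measured to form the ratio, so the total is available if the values are kept.
- A reader might infer that the total is simply the right replacement. Steps 3 and 4 show otherwise. It also moves with any dietary nitrate, and it loses the ratio's insensitivity to dilution.
- A reader might infer from the self-filled container that nitrate turns to nitrite before freezing and distorts the ratio. The article gives no transit times, preservation details or concentrations, and such handling detail commonly sits in the full protocol. That is not a finding here.
- A reader might infer that the biomarker research question fails. That question asks about a marker of oxidative stress, a role the article gives to 8-hydroxy-2′-deoxyguanosine. Nor does any section say that nitrite/nitrate results will select a marker for the large trial.

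**Conclusion.** The point holds in a limited form. The listed measurement is a ratio, the planned interpretation is an amount, and the first does not identify the second. If both products rise in proportion, the ratio stays still. If they do not, its movement can be read as production only with assumptions that the article does not supply.

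That conclusion rests on algebra alone. The numerical cases use assumed constants and show only what can happen, and the dietary route is an assumption from outside the article.

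The impact is minor. Biomarkers appear in neither the primary nor the secondary aims, and the sample size and the covariance analysis of MD score are unaffected. What changes is the conclusion that this one exploratory outcome can carry.

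**What to change.** In Biomarker analysis:

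1. State that nitrite and nitrate are kept as separate values, and analyse their total alongside the ratio. Scale the total for urine dilution where a dilution measure is available. Where none is, report it unscaled and say so.
2. Do not interpret the ratio as production. Limit the conclusion to an association of urinary nitrite/nitrate with MD score.
3. State that both total and ratio could also reflect dietary nitrate, as an assumption, and show FFQ intake at baseline and 24 weeks beside them.
4. Reconcile the marker sentence with the measurement sentence, so that one defined quantity is the outcome. Check the gas name against the full protocol at the same time, since the sentence leaves unclear how nitrite/nitrate relate to the products of the gas.

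**Cost.** Mostly wording and one extra calculation on values that forming the ratio already requires. There are two real downsides. The total depends on urine dilution, which the ratio cancels, and the section lists no dilution measure, so scaling may need an additional determination. The claim made for the marker also becomes weaker.
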